#### **6.5.1 Overdose**

Experience with ulipristal acetate overdose is limited. Single doses up to 200 mg and daily doses of 50 mg for 10 consecutive days were administered to a limited number of subjects, and no severe or serious adverse reactions were reported.

#### **6.5.2 Contraception**

Concomitant use of UPA with progestagen-only pills, a progestagen-releasing intrauterine device or combined oral contraceptive pills is not recommended. Although a majority of women taking a therapeutic dose of ulipristal acetate are anovulatory, where contraception is required, the woman will be asked to use a barrier method with spermicidal foam/gel/film/cream/suppository, in line with MHRA contraception guidelines.

#### **6.5.3 Potential drug interactions**

Ulipristal acetate is not recommended for patients receiving P-glycoprotein (P-gp) substrates (e.g. dabigatran etexilate, digoxin).

Co-administration of moderate or potent Cytochrome P450 (CYP3A4) inhibitors (e.g. erythromycin propionate, ketoconazole, ritonavir, nefazodone) may lead to significant changes in plasma levels of ulipristal acetate and so women requiring potent drugs are not eligible for UCON and the use of UPA in those requiring moderate potency CYP should be reviewed carefully. Concomitant use of mild CYP3A4 inhibitors is acceptable and no dose adjustment of UPA is considered necessary.

Patients receiving concomitant Cytochrome P450 (CYP3A4) inducers may have reduced plasma levels of UPA and so concomitant use potent CYP3A4 inducer, such as anti-convulsants (e.g.

carbamazepine, phenytoin) or anti-infectives (e.g. rifampicin, nevirapine) or St John's Wort is not recommended.

## **6.6 KNOWN ADVERSE REACTIONS FOR ULIPRISTAL ACETATE**

A full list of known adverse reactions for UPA is given in SmPC Reference Document, whilst specific issues of concern are detailed here.

### **6.6.1 Endometrial changes**

In 10-15% of women, thickening (> 16 mm by ultrasound or MRI at end of treatment) of the endometrium may occur. In addition, changes in the histology of the endometrium (PAECs) may be observed, that are different to endometrial hyperplasia. These changes are reversible after treatment cessation. More evidence regarding PAEC is discussed in Section 1.2.

### **6.6.2 Bleeding pattern**

Participants should be informed that treatment with ulipristal acetate usually leads to a significant reduction in menstrual blood loss or amenorrhea within the first 10 days of treatment. Should the excessive bleeding persist, participants should notify their GP. Menstrual periods will generally return within 4 weeks after the end of the treatment course.

### **6.6.3 Other hormonal adverse events**

Hot flushes were reported by 12.7% patients on average but the rates varied across trials. In PEARL II, the rates were 24% (10.5% moderate or severe) for UPA and 60.4% (39.6% moderate or severe) for leuprorelin-treated patients. In PEARL I, the rate of hot flushes was 1.0% for UPA and 0% for placebo.

Functional ovarian cysts were observed during and after treatment in 1.5% of patients and in most of the cases spontaneously disappeared within a few weeks.

### **6.6.1 Liver Injury (unconfirmed adverse reaction currently under investigation)**

Five reports of serious liver injury, including four cases of hepatic failure needing liver transplantation, have been reported worldwide in women using UPA for uterine fibroids.

Women with severe hepatic impairment are excluded from the trial. Participants receiving UPA will undergo monthly liver function tests to monitor for signs of liver injury (see 6.5 for further details).

## **6.7 SPECIAL WARNINGS AND PRECAUTIONS FOR USE FOR LEVONORGESTREL**

### **6.7.1 Fitting of the LNG-IUS**

LNG-IUS fitting should ideally be performed by an experienced gynaecologist at the second clinic appointment. If this is not possible, a prescription can be given to enable the woman to go to a

sexual health clinic or her GP, for the coil to be fitted by a clinician as per standard clinical care and current service provision.

Perforation of the uterine corpus or cervix may occur, most commonly during insertion. This may be associated with severe pain and continued bleeding. If perforation is suspected the system should be removed as soon as possible and reported as a trial treatment withdrawal to the UCON Trial Office.

The insertion tube for LNG-IUS has been designed to minimise the risk of infections. Women should be told to be aware of symptoms and signs suggestive of pelvic infection and to go to her GP if at all concerned.

The RCOG guidelines suggest a women should be re-examined six weeks after insertion and further examinations should be performed where clinically indicated, but this will be left to the discretion of the gynaecologist to advise.

### **6.7.2 Potential drug interaction**

The metabolism of progestogens may be increased by concomitant use of CYP3A4 inducers but the influence on these drugs on the contraceptive efficacy of the LNG-IUS has not been studied. However, it is not believed that CYP3A4 inducers will have a major importance, due to local mechanism of action of LNG-IUS.

## **6.8 KNOWN ADVERSE REACTIONS TO LEVONORGESTREL**

Undesirable effects are more common during the first months after the insertion, and subside during prolonged use. A full list of known adverse reactions for LNG-IUS is given in Table whilst specific issues of concern are detailed here.

### **6.8.1 Bleeding irregularities**

LNG-IUS usually achieves a significant reduction in menstrual blood loss in 3 to 6 months of treatment. Irregular bleeding/spotting may occur during the first months of therapy in pre-menopausal women. Some women's periods may even stop completely. Increased menstrual flow or unexpected bleeding may be indicative of expulsion.

### **6.8.2 Possibility of pregnancy**

The LNG-IUS, when inserted properly, is an extremely effective contraceptive. The possibility of pregnancy should be considered in amenorrhoeic women if there are other symptoms, and expulsion should be excluded.

The absolute risk of ectopic pregnancy in LNG-IUS users is low. However, when a woman becomes pregnant with the LNG-IUS in situ, the relative likelihood of ectopic pregnancy is increased. The possibility of ectopic pregnancy should be considered in the case of lower abdominal pain - especially in connection with missed periods or if an amenorrhoeic woman starts bleeding.

## 6.9 OTHER MEDICATIONS

### 6.9.1 Permitted Medications

Drugs not listed as prohibited or have potential to interact (see Sections 6.5.3 and 6.7.2) are allowed.

### 6.9.2 Prohibited Medications

In order not to confound the effects of the trial treatments, the following should not be prescribed or taken by any participants whilst on trial treatment. Should the women withdraw or be excluded from the trial treatment but continue to provide data, continued regular use of below drugs should be noted. For patients who are 'coming off' some medications pre-randomisation then please refer to the wash out times specified in section 6.9.3.

- Mefenamic acid
- Tranexamic acid
- GnRH analogues
- Progestagen-only contraceptive
- Any progestagen-releasing intrauterine device (except if allocated within UCON)
- Any combined oral contraceptive pills

### 6.9.3 Wash out times

- |                                                                                |        |
|--------------------------------------------------------------------------------|--------|
| • GnRH agonist/ antagonist: 3 to 6 month sustained-release preparation         | 52 wks |
| • Immediate or monthly sustained-release GnRH agonist preparation              | 26 wks |
| • Sex steroid: Progestins (systemic/ progestin-releasing intra-uterine system) | 4 wks  |
| • Oral contraceptive                                                           | 4 wks  |
| • Mefenamic acid or antifibrinolytic drugs such as tranexamic acid             | 1 wk   |

## 7 STUDY ASSESSMENTS

Due to the different nature of the IMPs, the timing and format of the study assessments will differ slightly between the groups.

### 7.1 STUDY ASSESSMENTS OVERVIEW

A summary of actions and assessments undertaken, and data collected, at each time point is shown in **the Trial Schema (**

## Appendix 1: TRIAL SCHEMA

**Appendix 1).** Women who have consented and randomised to the mechanistic sub-study will have additional assessments that relate to this study only, but will otherwise complete the same study outcome as those randomised to the UPA group and be followed up in exactly the same manner.

## **7.2 TIMING OF STUDY ASSESSMENTS**

The overriding principles for the timing of the follow-up study assessments are:

1. The patient completed questionnaires should ideally be completed in the final week of each on-treatment cycle or equivalent for the UPA group, and at an equivalent time for the LNG-IUS group. Participants who stop treatment should complete questionnaires as originally scheduled (i.e. approximately 3, 6 and 12 months post randomisation).
2. The menstrual blood loss diary whilst on treatment should ideally be completed over the final four weeks of each treatment cycle in the UPA group, and at an equivalent time for the LNG-IUS group. The UPA group will also be asked to complete the diary during the first 4 weeks off treatment before the start of the next treatment cycle (as per the cyclical regime stated in section 6.2.1).
3. The post-treatment endometrial biopsy should be completed after 4 weeks off treatment, which would be approximately 48 weeks after UPA was commenced.
4. Should PAECs be observed in the post-treatment biopsy specimen in the UPA group, a repeat endometrial biopsy should be taken around 13 weeks after the completion of treatment, and then again around 26 weeks post-treatment if PAECs persist.
5. The endometrial biopsy, blood sample and MRI at time point 26 weeks in the sub-study should be in the final week of the second UPA cycle, to determine the features of the endometrium while receiving treatment.

A timeline for the treatment regimens and completion of the assessments is shown in Figure 4.

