## **2.2 RCT OUTCOMES**

### **2.2.1 Primary outcome**

The primary outcome measure is the condition-specific Menorrhagia Multi-Attribute Scale (MMAS) designed and validated to capture the impact of HMB on women's day-to-day life (19). HMB is a subjective problem and quality of life is affected by practical difficulties and the impact on social life, psychological wellbeing, physical health, work routine and family life. The menorrhagia multi-attribute utility assessment (MMAS) questionnaire attempts to capture the consequences of HMB on these domains with 6 questions each with 4 levels of response. Summary scores range from 0 (not affected) to 100 (worst affected). The primary time point for analysis will be at 12 months.

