## **6.2 DOSE AND DELIVERY OF IMPS**

### **6.2.1 UPA**

**Randomisation was suspended on 12 February 2018 on account of a USM requirement from the MHRA (12th February 2018).**

**Participants already randomised to receive UPA may complete their current 12 week course No further courses will be initiated.**

**[Procedure adopted prior to USM:** Those allocated to UPA will receive proprietary ulipristal acetate 5mg, orally, once daily.

A single tablet must be taken orally once daily with or without food, at approximately/ or as close as possible to the same time each day. The participant should start taking UPA within the first five days of starting their menstrual bleeding.

If a participant misses a dose, she should take UPA as soon as possible. If the dose was missed by more than 12 hours, the participant should not take the missed dose and simply resume the usual dosing schedule.

Women will be instructed to take UPA in 3 courses according to the following cyclical regime ( $\pm$  5 days):

1. One 5mg tablet of UPA to be taken daily for 12 weeks then stopped for 4 weeks, when light vaginal bleeding may occur (withdrawal bleed).
2. After 4 weeks off treatment, regardless of whether they experience a withdrawal bleed, they should recommence UPA 5mg daily for another 12 weeks, then stop for 4 weeks, when they will expect to have a withdrawal bleed.
3. Repeat as for treatment courses (2).

We have chosen this regime as women and their clinicians will likely prefer a regime that has only one menstrual bleed between treatment courses and thus our study will be able to provide valuable data on this aspect of UPA treatment. ]

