### **8.1.7 End of Study Visit Form**

The research nurse will contact each participant to arrange their end of study visit (follow-up assessment) which will ideally take place between approximately weeks 49 and 57. The assessment will include confirmation of whether there was a change to treatment during trial participation, satisfaction with treatment, participant rating of treatment and whether they would recommend to a friend and onward treatment intention.

Participants in the LNG-IUS group will undergo an ultrasound and have a blood sample taken. Participants in the UPA group will undergo an ultrasound, endometrial biopsy and have a blood sample taken.

For participants in the UPA mechanistic sub-study will undergo an ultrasound, endometrial biopsy, MRI scan and have a blood sample taken.

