### 8.5.2 Uterine and fibroid function

The aim of the MRI sub-study is to investigate the hypothesis that UPA will reduce blood flow and blood volume in the endometrium and myometrium in women with HMB. In particular, dynamic contrast enhanced MRI (DCE-MRI) and high spatial resolution structural MRI will be obtained in a subgroup of 20 women treated with UPA. DCE-MRI, combined with pharmacokinetic modelling, yields quantitative estimates of physiological parameters, including tissue blood flow, blood volume fraction and endothelial permeability, as well as volume fraction of the extracellular extravascular space. Structural MRI provides high resolution images suitable for structural segmentation and radiological evaluation that, when combined with design based stereological analysis (20), yield accurate and precise measurements of uterine and fibroid volume for early assessment of treatment response.

Scanning will be performed at baseline, and at 6 and 12 months following commencement of treatment. Scans will take place during the secretory phase of the menstrual cycle at baseline and in the week prior to the end of the second and third cycles of UPA, weeks 27 and 43 respectively.

Structural images will be evaluated clinically by an experienced radiologist, and stereological analysis performed to determine the volumes of the uterus and of any fibroids. Modern design based stereological methods will measure total volume of endo- and myo-metrial compartments, and

volume, type and location of individual fibroids, with mathematically predicted precision, on high resolution MR images.

Dynamic Contrast Enhanced (DCE)-MRI will be used to measure uterine tissue perfusion. Contrast agent concentration is modelled as exchange between the blood plasma and extracellular interstitial spaces, providing maps of tissue blood flow, blood and interstitial volume fraction and artery to tissue delay (i.e. lag) time. DCE-MRI data will be analysed using the well-established adiabatic approximation to tissue homogeneity (AAHT) model, to generate pharmacokinetic maps of blood flow, blood volume and extracellular extravascular volume fraction; these will be used to extract representative values for endometrium, junctional zone, outer myometrium and fibroid tissue.

Both MRI approaches are novel in the context of SPRM administration, so will be piloted in the first patients, who may require repeat scans with a refined protocol.

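### Protocol section 7.2 gives two inconsistent times for the primary 12-month MMAS, and which one applies depends on whether treatment has stopped

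*Protocol*

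**What the plan says.** Section 2.2.1 of the protocol fixes the endpoint: "The primary time point for analysis will be at 12 months".

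Section 7.2 item 1 says when the questionnaires, and so the MMAS, are collected. It contains two rules.

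- Women on treatment: "The patient completed questionnaires should ideally be completed in the final week of each on-treatment cycle or equivalent for the UPA group". LNG-IUS women are placed at a matching time.
- Women who stop: "Participants who stop treatment should complete questionnaires as originally scheduled (i.e. approximately 3, 6 and 12 months post randomisation".

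Section 6.2.1 gives the regimen that the first rule follows, three courses of "One 5mg tablet of UPA to be taken daily for 12 weeks then stopped for 4 weeks". UPA starts with a menstrual bleed, not on the day of randomisation.

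Two other sections bear on what the 12-month label means. Section 8.5.2 describes scans at 6 and 12 months and then places them "in the week prior to the end of the second and third cycles of UPA, weeks 27 and 43 respectively". Section 8.1.7 describes the end-of-study visit, "which will ideally take place between approximately weeks 49 and 57". Table 1 has a single approximate 12-month column for all of these assessments.

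**The concern.** The two rules in item 1 differ in date and in origin. One counts from the first tablet and ends with course 3; the other counts from randomisation and ends at 12 months. What moves a woman from one to the other is stopping treatment, which happens after randomisation and may be related to how well the treatment works. A primary endpoint should not have its measurement time set that way.

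The choice of date also matters for women who complete UPA. Section 6.6.2 says: "Menstrual periods will generally return within 4 weeks after the end of the treatment course". A woman who finishes course 3 is on drug at week 44 and about 8 weeks past her last tablet at week 52. If a site takes the endpoint name in 2.2.1 at face value and sends the questionnaire at 12 months, it measures a different state from the one that 7.2 intends.

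The urgent safety measure sharpens this. No new UPA course is started (Change of Treatment following USM), and women who stop remain in follow-up (Important Notice). The stopping rule therefore reaches UPA women more often, while LNG-IUS women still on treatment follow the on-treatment rule.

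**Working it through.** **Inputs.** Course 12 weeks, gap 4 weeks, three courses (6.2.1). Questionnaire in the last on-drug week, or at 12 months from randomisation after stopping (7.2 item 1). Primary time point 12 months (2.2.1). Lag from randomisation to first tablet: not given; assumed 0 to 4 weeks.

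**Step 1, the regimen in weeks from first tablet.**
- Course 1: weeks 0-12, off to 16.
- Course 2: weeks 16-28, off to 32.
- Course 3: weeks 32-44, off to 48.
- End of course 3 = 12 + 4 + 12 + 4 + 12 = 44. The last on-drug weeks are 11-12, 27-28 and 43-44.

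**Step 2, check against the protocol's own figures.**
- MRI in the week before the end of courses 2 and 3: stated as weeks 27 and 43 (8.5.2). Reproduced.
- Post-treatment biopsy after 4 weeks off drug: 44 + 4 = 48, stated as about week 48 (7.2 item 3). Reproduced.
- Third diary (8.1.2), from week 40: 28 days for LNG-IUS ends at week 44; 56 days for UPA ends at week 48. Consistent.

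**Step 3, the two rules compared.** Twelve months = 365.25 / 7 = 52.2 weeks. The gap is 52.2 - (44 + L), where L is the start lag in weeks.

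| L (assumed) | Last on-drug week, from randomisation | Gap to 12 months |
|---|---|---|
| 0 | 43-44 | 8.2 weeks |
| 2 | 45-46 | 6.2 weeks |
| 4 | 47-48 | 4.2 weeks |

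These are nominal dates; the regimen's tolerance of 5 days either way is not carried through. With L = 0, the earlier time points differ less: week 12 against 13.0 weeks for 3 months, and week 28 against 26.1 weeks for 6 months. The final, primary time point has the largest discrepancy.

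**Step 4, the other reading.** If the stopping rule means the unchanged schedule, and 12 months is shorthand for about week 44 as in 8.5.2, the gap is 0. The explanation in brackets in 7.2, which counts months from randomisation, is then wrong.

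**Step 5, what the 12-month label covers.** In Table 1 one column holds the questionnaires (about weeks 43-44), the MRI (week 43), the biopsy (about week 48), and the ultrasound and bloods (end-of-study visit, weeks 49-57). The label spans weeks 43 to 57, so it cannot by itself settle when the MMAS is due.

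**Step 6, imbalance between arms.** On the literal reading, the shift in the treatment difference from timing is roughly the excess proportion of UPA women under the stopping rule multiplied by the mean MMAS change between the two dates. The documents give neither quantity.

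**The case against.** The strongest reply is that this is loose wording. The protocol uses 12 months for about week 43 in 8.5.2, and the Table 1 column is marked approximate. On that usage women who stop simply keep their dates. The UPA clause also says or equivalent, which may cover women no longer in a course, and both rules are softened by ideally and approximately. This stands as a possible reading, and it is why the gap is given as 0 to about 8 weeks. It does not clear the text: on that reading the bracketed months in 7.2 and the endpoint name in 2.2.1 are both inaccurate, and soft wording leaves the primary time point less fixed. The timeline, pathway and schema figures are not available here and may show a target week. The timeline and schema are headed as applying before the safety measure, so the text still has to be consistent.

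Three stronger readings are tempting and are not supported.

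- A reader might infer that the rule itself treats the arms differently. It does not. The text runs "and at an equivalent time for the LNG-IUS group. Participants who stop treatment", so LNG-IUS is aligned with UPA and the stopping rule covers participants in both arms. Dependence on arm is indirect, through the safety measure, and arises only on the literal reading.
- A reader might infer that the two dates turn an on-drug value into an off-drug value for women who stop. A woman who stopped early is off UPA at both dates, and may be on an alternative HMB treatment. Analysis by intention to treat accepts that. The on/off contrast applies to women who complete course 3.
- A reader might infer that the off-drug phase is never observed, and scale the 13-point target difference by the share of the cycle on drug. Only the questionnaires miss that phase; the UPA bleeding diary covers it (7.2 item 2, 8.1.2). Nothing in the documents supports such scaling, and the 13 points come from a trial of LNG-IUS against standard treatment.

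**Conclusion.** The point holds as an inconsistency in how the primary endpoint is timed. Item 1 of section 7.2 names two dates with two origins, and treatment status after randomisation decides between them. Read literally, they are about 8 weeks apart, or about 4 to 8 weeks under the assumed start lag of 0 to 4 weeks. Read charitably the gap is zero, but then the protocol misstates the timing in 7.2 and misnames the endpoint in 2.2.1. Either way the text needs correcting.

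Since the safety measure, the stopping rule falls mainly on the UPA arm, so a timing imbalance between arms is possible. Its size cannot be computed from the documents, and no bias of a given magnitude is shown. The sample size is unaffected.

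**What to change.** Reconcile the two sentences of section 7.2 item 1. State one target week counted from randomisation, with one window, for the primary MMAS. Apply it in both arms, whether or not treatment has stopped, including women stopped by the safety measure. Use that week as the endpoint's name in 2.2.1, the trial summary and Table 1 in place of 12 months.

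If the aim is to keep continuing UPA users in their last on-drug week, the table above shows what the window must contain: weeks 43 to 48 from randomisation for start lags of 0 to 4 weeks. The choice of week is for the trial team; what matters is that there is only one.

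Record the actual assessment week and the weeks since the last tablet for each questionnaire, so that a sensitivity analysis of the primary result can use them. A further MMAS at the end-of-study visit would be an optional addition and is not needed to resolve the inconsistency.

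The cost is protocol wording, questionnaire mailing dates and two recorded items. No dose or treatment rule changes. It should be settled before the remaining final questionnaires are collected.

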#### 8.1.2 Menstrual Diary

The standard pictorial blood assessment chart (PBAC) (14) will be given to the woman at the first clinic visit to allow her to complete during her next menstruation and return it at the second clinic visit, which should be scheduled to be at least 4 weeks after the first.

Both UPA and LNG-IUS may induce amenorrhea (absence of bleeding) in some women, so whilst on treatment, the concept of a regular cycle is problematic. A modified menstrual diary, with ordinal questions regarding bleeding each day, will be used to establish the degree of menstrual bleeding. This will be completed for 28 days from week 8 for women in the LNG-IUS group and for 56 days

from week 8 in the UPA group, then again at week 24 and week 40, for 28 and 56 days for the LNG-IUS and UPA groups, respectively.

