### **9.2.2 Secondary analysis**

MMAS scores at three and six months follow-up will be analysed as per the primary analysis. Data from the other continuous measures (UFS-QOL, EQ-5D, ICE-CAP, VAS and SAQ) will be analysed in a similar fashion to the MMAS scores. Further exploratory analysis using a repeated measures model will also be used for these continuous measures to examine differences over all time-points. Bleeding diary scores will be converted into categories including the proportion with amenorrhoea ( $=0$ ) and heavy bleeding ( $\geq 100$ ). They will be analysed using relative risks and chi-squared tests. Time from randomisation to surgery (hysterectomy or endometrial ablation) will be analysed by log-rank test with a Cox Proportional Hazard (PH) model also built if the assumptions of proportionality are met. Other outcome measures (Likert responses, Likert ordinal responses, satisfaction) will be analysed using standard methods (tests for trend, absolute and relative risks). Paired t-tests will be used to examine differences within groups over time.

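### The 6-month sub-study biopsy, taken only in UPA women, falls inside the bleeding diary shared by both arms and in the questionnaire week, so procedure bleeding can lower UPA amenorrhoea at 6 months

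*Protocol*

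**What the plan says.** **Biopsy.** The fifth item of section 7.2 sets the date: "The endometrial biopsy, blood sample and MRI at time point 26 weeks in the sub-study should be in the final week". The week meant is the last one of UPA course 2, so that the endometrium is seen on treatment. Section 5.2 offers the extra procedures at the Edinburgh site and says they apply only to women allocated to UPA. Sections 4.1 and 9.3 put the number at about 20. Table 1 gives LNG-IUS women no biopsy after screening.

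**Diary.** The second item of section 7.2 says: "The menstrual blood loss diary whilst on treatment should ideally be completed over the final four weeks of each treatment cycle in the UPA group". LNG-IUS women keep it at a matching time. Section 8.1.2 gives the lengths. On the first diary it says: "This will be completed for 28 days from week 8 for women in the LNG-IUS group and for 56 days", where the longer period is the one for UPA. On the later diaries it says: "then again at week 24 and week 40, for 28 and 56 days for the LNG-IUS and UPA groups".

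**Questionnaires.** Section 7.2, item 1 places them ideally in the final on-treatment week of each course, and at an equivalent time for LNG-IUS.

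**Who is compared.** Section 7.1 (its text runs on under the Appendix 1 heading) says sub-study women "will otherwise complete the same study outcome as those randomised to the UPA group and be followed up in exactly the same manner".

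**Scoring.** Section 9.2.2: "Bleeding diary scores will be converted into categories including the proportion with amenorrhoea", defined as a score equal to 0, and heavy bleeding, defined as 100 or more. Both are analysed by relative risks and chi-squared tests. Menstrual blood loss at 3, 6 and 12 months is a secondary objective (section 2.1.2).

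**The concern.** A trial procedure done in one arm only sits inside the period in which bleeding is counted in both arms. The diary asks about bleeding each day, and the protocol does not separate bleeding caused by a biopsy from menstrual bleeding. Because the amenorrhoea cut-off is exactly zero, a single day of recorded spotting is enough to reclassify a woman. Any such effect can only reduce UPA amenorrhoea and cannot touch LNG-IUS, so it is a one-sided bias caused by the assessment schedule and not by either treatment.

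The 6-month pain scores and MMAS are exposed in a weaker way. They are due in the biopsy week, and nothing says they come first.

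**Working it through.** **1. Calendar.** Inputs: three courses of 12 weeks on and 4 weeks off (section 6.2.1).
- Reproducing the plan's own figure: 3 × (12 + 4) = 48 weeks, as section 7.2 gives for the post-treatment biopsy.
- Courses run over weeks 0-12, 16-28 and 32-44. The final on-treatment weeks are 11-12, 27-28 and 43-44.
- Diaries start at weeks 8, 24 and 40. LNG-IUS (28 days): weeks 8-12, 24-28 and 40-44. UPA (56 days): weeks 8-16, 24-32 and 40-48.

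**2. Overlap.**

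| Biopsy | Week | Shared diary | Questionnaire week | Overlap |
|---|---|---|---|---|
| Sub-study, 6 months | 27-28 | 24-28 | 27-28 | Full |
| End of treatment, all UPA women | about 48 (visit 49-57) | 40-44 | 43-44 | None; at least 4 weeks later |

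The week-48 biopsy only touches the end of the UPA off-treatment diary, which has no LNG-IUS counterpart. Section 7.2 also labels the sub-study visit 26 weeks, and section 8.5.2 gives week 27 for the matching MRI. These should be reconciled, but each lies within weeks 24-28.

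**3. Size at 6 months.** Let p be true UPA amenorrhoea, m the number biopsied, N the UPA arm and q the share of biopsied, otherwise amenorrhoeic women who record procedure bleeding.
- Observed amenorrhoea = p × (1 − q × m/N). Fall = p × q × m/N.
- m = 20 (sections 4.1 and 9.3). N = 220/2 = 110 (sections 4.1 and 5.6.2). Share exposed = 20/110 = 18%.
- p = 70% is an assumption. Section 1.1 reports over 70% in two earlier trials in women with fibroids.
- q is an assumption. The protocol gives no rate of bleeding after biopsy.

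| q | Observed | Fall | Relative risk multiplied by |
|---|---|---|---|
| 25% | 66.8% | 3.2 points | 0.955 |
| 50% | 63.6% | 6.4 points | 0.909 |
| 100% | 57.3% | 12.7 points | 0.818 |

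For example, 0.70 × 0.50 × 20/110 = 0.064.

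**4. Range.** With q = 100%, p from 50% to 90% gives a fall of 9.1 to 16.4 points. If only 86 UPA women are evaluable (the figure in section 9.1.1) and all 20 are among them, the share is 20/86 = 23%, and the fall at p = 70%, q = 100% is 16.3 points. The fall is proportional to m, so it is smaller if fewer than 20 women reach this biopsy.

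**The case against.** **Left to the SAP.** Only the protocol is at hand, section 9.2 promises a full SAP, and diary scoring rules usually belong there. This is fair for the detail of the remedy. It does not remove the point, because the protocol itself fixes both the timing and the zero cut-off, and these two together create the bias.

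**Small and uncertain.** One centre, about 20 women and one secondary time point are involved. The post-biopsy bleeding rate is assumed, and the scoring of the modified diary is not shown. All of this stands. Heavy bleeding at 100 or more is also much less sensitive than a score of 0.

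**Stronger readings that a reader might infer, and why the protocol does not support them.**
- *The primary result is biased.* On the planned schedule the 12-month MMAS, pain scores and on-treatment diary come before the week-48 biopsy.
- *Women stopped early by the safety measure are affected too.* A repeat biopsy 13 weeks after course 1 or 2 would fall at week 12 + 13 = 25 or 28 + 13 = 41, inside diary windows. But those women are 13 weeks off UPA, and section 6.6.2 says periods generally return within 4 weeks, so most would not score 0 in any case. Section 7.2 keeps stopped women on schedule explicitly for questionnaires only. Overlap is possible, including for women who stop mid-course, but it is not established.
- *The false-positive rate is known.* With 70% amenorrhoea in both arms and 88 evaluable per arm (110 × 0.8), a two-proportion test would reject in about 7%, 15% or 43% of trials for the three values of q. The protocol gives no amenorrhoea rate for LNG-IUS, and the last figure needs every biopsied woman to bleed.

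**An obvious remedy would mislead.** Masking the biopsy day and the week after it would remove up to 7 of 28 diary days (25%) in UPA women only. That makes a score of 0 easier to reach and favours UPA. This objection is right, and the fix avoids it.

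**Conclusion.** The point holds for the 6-month sub-study biopsy. As scheduled, it overlaps the shared diary completely and shares a week with the 6-month questionnaires. It is done in one arm only, and it feeds an endpoint that any recorded bleeding can change. The direction is against UPA. The size is unknown: 3.2 to 12.7 points on UPA amenorrhoea at 6 months for assumed bleeding rates of 25% to 100%, with 70% true amenorrhoea and 20 of 110 women exposed. This also assumes that the on-treatment 28 days are what is compared and that a day of spotting gives a non-zero score. Effects on bleeding days and pain at 6 months are plausible but not quantified. The concern is confined to 6-month secondary outcomes and does not reach the primary analysis on the planned schedule.

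**What to change.** 1. **Section 7.2:** state that the 6-month questionnaires are completed before the biopsy in any woman still to have it. Sub-study recruitment is complete and no new course may start, so this reaches only women already in course 2.
2. **Section 9.2.2 or the SAP:** add a sensitivity analysis of the 6-month diary outcomes, in one or both of these forms:
   - Score the same pre-biopsy days in both arms, for example the first 21 days from week 24 (weeks 24-27). Check this against the actual biopsy dates; if any biopsy was earlier, shorten the window equally in both arms.
   - Restrict both arms to women who did not agree to the biopsy sub-study. Agreement is recorded before allocation and is a minimisation factor (section 5.6.1), so the comparison stays randomised.
3. Do not mask diary days only in biopsied women.

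Biopsy timing does not change. The cost is a few sentences and little programming. The sensitivity analysis has either 7 fewer diary days per woman or fewer women: roughly 110 − 20 = 90 per arm before loss to follow-up, if about 20 in each arm had agreed to the biopsy.
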